## Abstract

**Background:**

Treatment for displaced proximal humeral fractures is still under debate. Few studies exist at the highest level of evidence. Although reversed total shoulder prosthesis has gained popularity and showed promising results in the treatment for proximal humeral fractures in the elderly patients, no randomized controlled trials exist to the authors’ knowledge.

**Methods/Design:**

This study is a randomized semi-blinded controlled multicenter trial designed according to the Consort statement and the recommendations given by the Cochrane reviewers for proximal humeral fractures. The study will investigate whether a reversed total shoulder prosthetic replacement gain better functional outcome compared to open reduction and internal fixation using an angular stable plate in displaced three- and four parts proximal humeral fractures after two and five years follow-up.

Participants are aged 65–85 admitted in seven different hospitals with a displaced proximal humeral fracture according to AO-OTA type 11-B2 or 11-C2. The intervention group is surgical treatment using a reversed total shoulder prosthesis (Delta X-tend) compared to open reduction and internal fixation with an angular stable plate (Philos) and thread cerclage in the control group. 60 patients will be randomized to each group.

The primary outcome is shoulder function (Constant score). Secondary outcomes will be patient self-assessment form (Oxford shoulder score), a quality of life questionnaire (15D score) and resource implications (cost-effectiveness). Follow-ups take place at 3, 6, 12 and 24 months, and five years. The trial design is semi-blinded with blinded physiotherapists performing the functional testing of patients at all follow-ups.

Randomization to treatment groups is electronic online, by independent supervisor (web-CRF). The recruitment of patients started at January 1.st 2013. Inclusion of 120 patients during three years is expected.

**Discussion:**

This semiblinded trial include a high number of patients compared to existing randomized trials in this field. To our knowledge and according to ClinicalTrials.gov, this is the first study that compare these two treatments for a displaced proximal humeral fracture in elderly patients. This may provide important information to help the surgeon to decide the best treatment in the future.

**Trial registration number:**

ClinicalTrials.gov Identifier: NCT01737060

**Electronic supplementary material:**

The online version of this article (doi:10.1186/1471-2474-15-323) contains supplementary material, which is available to authorized users.

## Background

Treatment for displaced proximal humeral fractures is still under debate several decades after the first recommendations for “modern treatment principles” were given by Neer [1, 2]. Meta-analyses have been difficult to perform due to different methodological approaches, treatment modalities and rehabilitation programs. According to the last Cochrane review, including 16 small randomized trials at the highest level of evidence and a total number of 801 patients, best treatment has not yet been ruled out. The authors of the Cochrane review emphasize that new trials must take into account important issues like methods of randomization, blinding and duration of follow-up, as well as standard and validated outcome measures, patient assessed functional outcomes and resource use assessments. New trials should also meet the criteria for design and reporting according to the Consort statement [3, 4].

Our intention is to design a randomized study between two methods of surgical treatment meeting the recommendations given by these authors.

Fractures of the proximal humerus normally account for about 5% of all fractures. Most patients sustaining these fractures are women above the age of 60. The incidence of the proximal humeral fracture has been reported to increase with age during several decades, also based on the age-adjusted incidence [5–8]. Ageing of the world population will clearly increase the number of future fractures, as high age, incidence of falls and osteoporosis are the main risk factors [9–12]. Fractures in the elderly represent in general a considerable burden to the patients in terms of pain, loss of function and even mortality, and to the society generating costs in different aspects [13]. Physical disabilities caused by fractures of the proximal humerus also make self-care and independent living difficult, thus interfering with quality of life [14]. In light of this, fractures in the elderly will become increasingly important in the future.

Although numerous studies exist dealing with proximal humeral fractures, most of them represent level IV evidence [15]. Thus, interpretation must be made with caution and evidence is at present too limited to support secure recommendations for treatment, even including if surgical treatment is superior to conservative for severely displaced fractures. The number of level I and II trials in this field are few. In our department we recently completed a single center randomized controlled study of displaced proximal humeral fractures; an angular stable plate was compared to conservative treatment. After two years follow-up we could not detect any significant differences between surgery and conservative treatment with regard to physical functioning and health-related quality of life [16, 17]. Nevertheless, there is evidence that the rate of surgical treatment has increased significantly in the period from 1999 to 2005 [18].

The proximal humeral fracture groups comprise two-, three,- or four part fractures: non-displaced, displaced or displaced with dislocation (AO-OTA type A,B and C) [19]. Many proximal humeral fractures are minimally displaced, and should not be considered for surgical treatment. About one fifth are displaced 3- and 4 part fractures (AO-OTA group B2 and C2) [7]. In these fractures many surgeons perform operative treatment, even if this has not been proven superior to a conservative approach except from in certain displaced fracture dislocations, where surgery may be favorable [3]. However, most orthopaedic surgeons agree that classification and differentiation of the main groups of proximal humeral fractures are important for treatment decision making, as prognosis and the technical challenges depend on the fracture displacement and comminution [20, 21].

If surgery is decided, the most frequent treatment modalities are open reduction and internal fixation with an angular stable plate, a locked intramedullary nail, or in some patients minimally open surgery with screws, threaded pins and sometimes cerclage wires. Shoulder hemi-artroplasty has also been widely used [22–32]. Although numerous surgical options exist for the displaced fractures, none has yet proven to be superior [3, 33–35]. Also, several complications and impaired shoulder function are reported after different types of surgical treatment [36–43].

The early reports of treatment with ORIF using angular stable plates were promising [44]. Later, however, it has become evident that although the angular stable implants contributed to the surgical management of severely displaced fractures, several problems and pitfalls stayed unsolved. The method of fixation utilizing an angular stable plate caused a disappointing number of complications, as cut-out of screws into the joint space, avascular humeral head necrosis, non-union, and varus malalignment [45–49]. Some of these complications are caused by poor surgical technique, and may be avoidable [50]. Supplemental tension band fixation and restoration of the medial calcar may improve outcome and decrease the incidence of hardware-related complications [20, 22, 51].

Head replacement or shoulder hemi-artroplasty (HA) has been used as a treatment option for three decades, and has been claimed a better option than open reduction and fracture fixation in certain severely displaced and dislocated intracapsular fractures, even though the evidence is still not conclusive. Some related important problems are well known: Poor rotator cuff status and non-union of the tubercles. If these main problems are avoided, patients may have a good outcome with these implants [41]. In the elderly patient suffering a proximal humeral fracture, however, the status of the rotator cuff frequently is poor [42, 43, 52, 53]. A recent randomized study concluded that head replacement did not prove better than conservative treatment [35], and several other authors also report unsatisfactory results with hemi-arthroplasty; Loss of ROM, non-union of tubercles in as many as 50% of the patients in some series and poor quality of the rotator cuff result in inferior functional outcome [28, 41, 54, 55].

A more recent treatment option for displaced proximal humeral fractures is the reverse total shoulder artroplasty (RTSA). It was introduced nearly 20 years ago in treatment of acute proximal humeral fractures [56]. During the last decennium the use of RTSAs has increased, both as a salvage procedure after failed hemi-artroplasty but also in the primary fracture care. RTSA has gained popularity and has showed promising results in the treatment for proximal humeral fractures in the elderly patients [57–59]. A small level 2 study was recently reported [39], concluding that RTSA showed similar outcome to HA, but functional outcome was more predictable. The advantage of the concept is less dependence on a normal rotator cuff, as the elderly population frequently suffer asymptomatic degenerative cuff tears leading to a poor prognosis [60]. However, problems with RTSA have been reported, mainly instability, poor rotation and fatigue of the deltoid muscle with time [56]. Also, radiological notching of the glenoid is frequent, but has not proven clinically important in the older Delta III prosthetic designs [61]. Due to these problems and complications the RTSA has until recently only been advocated in older patients [37]. Recently improved prosthetic designs possibly have reduced the problem of notching, due to overhang of the scapular component [62].

### Aims – hypothesis

#### Primary objective

The study will investigate whether a reversed total shoulder prosthetic replacement gain a better functional outcome compared to open reduction and internal fixation using an angular stable plate in severe displaced proximal humeral fractures.

We aim to conduct a high quality randomized controlled trial according to the recommendation from the Cochrane authors. Standard and validated outcome measures, patient assessed functional outcomes and resource implications like cost-effectiveness of these surgical methods will be addressed.

#### Secondary objective

Quality of life will be measured with the 15D score [63], and calculations of QALY and cost during hospital stay and two years follow-up. Further outcomes are radiographic results and the Oxford shoulder score [64].

#### Hypothesis

We aim to establish if treatment with reverse total shoulder artroplasty (RTSA) gain better functional outcome according to the Constant shoulder score compared to open reduction and internal fixation with an angular stable implant at two and five years of follow-up [65, 66].

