### Primary outcome: Constant score

The score originally described by Constant and Murley will be used to evaluate the functional outcome [65]. Maximum score for each shoulder is 100 points. Both shoulders will be rated and presented as absolute scores (CS). In order to reduce the influence of age the difference between the scores of the injured and the uninjured shoulder will be calculated. This difference is designated CSD (Constant Score Difference). Thus, normal function on the injured side will be zero. Measurement of strength will be performed according to recommendations given by the European Society of Shoulder and Elbow Surgeons ESSSE (http://secec.org/). The highest value of three measurements will be registered for the power score. There is no established minimal clinically important difference (MCID) for the Constant score, but 10 points is often regarded as suitable, although debated [67, 68].

The “Adjusted Constant score” (ACS) for the injured shoulder will also be calculated from the CS at the injured shoulder with adjustment for age and gender as a secondary outcome [66].

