### Power of the trial and sample size

To calculate the sample size we used the primary outcome Constant Shoulder Score with a range from zero to 100 points. Using the mean values from the injured shoulder in a similar population after proximal humeral fractures, SD equals18 according to clinical experience [16, 43]. There are two groups to be compared: Intervention group and control group. The minimal clinically important difference has been decided to equal 10 points. Level of significance (α) equals 0.05. Given a power of 0.80 (β) the number required in each group is 51 patients. Due to a predicted loss of included patients during follow-up, we aim to include 60 patients in each group.

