### Statistics

Statistical analyses will be performed with the SPSS 17.0 software or later version (SPSS Inc. Chicago, Illinois, USA). All outcomes will be reported as mean values and 95% confidence interval (95% CI) for both treatment groups and for each hospital separate, as well as for all hospitals together. In case of small data groups, bootstrapped 95% CI will be calcluated. Mean differences between the groups will be compared with independent *t*-test and Mann–Whitney test as appropriate at two and five years follow-up. Subgroup analyses for the two fracture groups B2 and C2 are planned to gain further information of effectiveness of treatment. Multiple imputation will be used to handle missing values. The QALY analysis from 15D outcome will be performed according to the specific 15D syntax for SPSS and completed with a one-way sensitivity analysis for each variable in the analysis.

The intention-to-treat principle will be adopted: Patients will be analysed according to their initial treatment group in case of cross over to the other group.

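### The primary hypothesis is tested at two and at five years with no ranking or success rule, but the stated alpha, power and 51 per group belong to a single test

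*Protocol article*

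**What the plan says.** **Time points.** The protocol article names two follow-up times for its main question in three places:

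- Abstract, Methods/Design: function is to be compared in "displaced three- and four parts proximal humeral fractures after two and five years follow-up".
- Hypothesis: the prosthesis is set against fixation on the Constant score, "compared to open reduction and internal fixation with an angular stable implant at two and five years of follow-up".
- Statistics: group means are compared by t-test or "Mann–Whitney test as appropriate at two and five years follow-up".

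None of these calls either time primary, orders them, divides alpha or says what counts as success.

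**Sample size.** Power of the trial and sample size gives one calculation: a difference of 10 points, SD 18, alpha 0.05. It concludes: "Given a power of 0.80 (β) the number required in each group is 51 patients". The SD is for the injured side: "Using the mean values from the injured shoulder in a similar population after proximal humeral fractures". No follow-up time is attached to the calculation. Sixty per group are to be enrolled to allow for losses.

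**Form of the score.** Under Primary outcome: Constant score, the absolute score comes first: "Both shoulders will be rated and presented as absolute scores (CS". The gap between the injured and uninjured shoulders follows: "This difference is designated CSD (Constant Score Difference". Only the age- and gender-adjusted score is labelled secondary.

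**The concern.** A hypothesis stated at two times needs a rule that turns two p-values into one conclusion. Without it, a trial that is positive at two years and not at five, or the reverse, has no pre-agreed reading. The two-year data arrive three years before the five-year data, so a split result is a practical prospect.

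The error rate and power quoted for the trial also depend on the missing rule. Counting a win at either time gives two chances of a false positive at 0.05 each. Requiring a win at both gives two chances to miss a real effect. A sample size built for one test describes neither situation.

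**Working it through.** **Inputs from the article.** Difference 10, SD 18, alpha 0.05, power 0.80, 51 per group, 60 enrolled per group (Power of the trial and sample size). Tests at two and five years (Statistics).

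**Assumptions, not in the article.** The correlation ρ between the two-year and five-year test statistics is varied from 0 to 0.9. For power, the true difference is 10 points at both times, with 51 per group analysed at each.

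**Step 1: reproduce the stated figure.**

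n = 2 × (1.96 + 0.842)² × 18² / 10² = 50.9, so 51 per group.

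This is one two-sided test with no allowance for a second. A one-sided test would give 41, which does not match. An exact t-test calculation gives 51.8, a trivial difference. The standardised effect is 10 / (18 × √(2/51)) = 2.81, and power is Φ(2.81 − 1.96) = 0.80.

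**Step 2: success at either time.**

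Type I error = 1 − P(|Z₁| ≤ 1.96 and |Z₂| ≤ 1.96). For ρ = 0 this is 1 − 0.95² = 0.0975. For ρ > 0 the correlated normal pair was simulated with 2 million draws.

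**Step 3: success at both times.**

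Joint power = P(Z₁ > 1.96 and Z₂ > 1.96), each Z having mean 2.81. For ρ = 0 this is 0.801² = 0.64.

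| ρ | Type I error, either time | Power, either time | Power, both times |
|---|---|---|---|
| 0 | 0.098 | 0.96 | 0.64 |
| 0.5 | 0.091 | 0.91 | 0.69 |
| 0.7 | 0.084 | 0.89 | 0.72 |
| 0.8 | 0.078 | 0.87 | 0.73 |
| 0.9 | 0.070 | 0.85 | 0.75 |

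Under the either-time rule, error exceeds 0.05 throughout while power stays above 0.80. Under the both-times rule, error stays at or below 0.05 while power is below 0.80 throughout.

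**Step 4: the form of the score.**

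The article gives no SD for CSD. With uninjured-side SD s and between-shoulder correlation r, SD(CSD) = √(18² + s² − 2 × r × 18 × s). For assumed values:

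- s = 8, r = 0.5: √(324 + 64 − 144) = 15.6, power with 51 per group 0.90.
- s = 12, r = 0: √(324 + 144) = 21.6, power 0.65.

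CSD could therefore be better or worse powered than the absolute score. The article does not settle which.

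**The case against.** **A single-test reading is available.** Both stated figures are correct for one test of the injured-shoulder score. A reader might infer that neither alpha nor power holds, but the table rules that out: whichever rule is adopted, only one of the two fails. Read literally, the hypothesis joins the two times with *and*, which favours the both-times rule and leaves alpha intact. That limits the criticism without removing it, because joint power is then below 0.80.

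**The four-test reading is inference.** Because CS and CSD both stand under the primary heading, a reader might count up to four primary tests and a still larger error rate. The article does not support this. The hypothesis names only the Constant score, and the sample size describes a 0-to-100 score of the injured shoulder, which is CS and not CSD. Nowhere is CSD called a confirmatory test. What remains is loose placement: one alternative form is labelled secondary and CSD is not.

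**Five-year attrition is a separate matter.** A reader might add that the allowance from 60 to 51 (1 − 51/60 = 15%) is too small for five years in this age group. The article gives no yearly loss rate and does not tie its power to five years, so any shortfall would rest on an assumed rate.

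**The analysis plan may settle it.** This is a condensed article, and test order and alpha allocation are often left to a fuller document. That is fair for detail. Here, however, the article itself states a two-time hypothesis beside a one-test sample size, and the two do not match as written.

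**Conclusion.** The point stands in a limited form. The hypothesis and its tests are fixed at two unranked times, while 0.05, 0.80 and 51 per group hold only for a single test of the injured-shoulder Constant score, with no time named. For the hypothesis as written, one stated figure fails: type I error is about 0.07 to 0.10 if either time suffices, or joint power is about 0.64 to 0.75 if both are needed.

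These ranges rest on an assumed correlation of 0 to 0.9 between the two times. The power range also assumes a true 10-point difference at both times with 51 per group analysed. The direction of each effect does not depend on the correlation chosen within that range.

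The unranked place of CSD is a lesser ambiguity, and no claim about its power can be made from the article.

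**What to change.** Name one primary analysis before results are known. One workable choice is the Constant score of the injured shoulder at two years, two-sided alpha 0.05. The form follows the sample size section. The two-year time is a proposal, since a reader might suppose that the calculation was made for two years but it names no time.

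Make the five-year score, and CSD at both times, secondary. If confirmatory claims are wanted from them, test them in a stated fixed order after the primary analysis. State that power 0.80 applies to the one primary test.

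This changes wording only and leaves 0.05, 0.80 and 51 per group as they are. The price is that the five-year result loses equal primary status.

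If equal status is wanted, alpha could be split. At 0.025 per time, n = 2 × (2.241 + 0.842)² × 18² / 10² = 61.6, so 62 per group, or 62 / 0.85 = 73 enrolled per group at the same 15% loss. With 51 analysed, power per test would be 0.71.

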## Methods/Design

### Study design

The design of the study is a multi-centre randomized controlled trial (RCT). Patients admitted to hospital with a displaced proximal humeral fracture in need of surgical treatment will be randomly allocated to two groups; Intervention group or control group. The design is semi-blinded for independent physiotherapists interviewing and testing the patients at three and six months, thereafter at one, two and five years.

### Interventions

**Group 1** is the intervention group. Patients will be treated surgically with a deltopectoral approach, resection of the supraspinatus tendon and insertion of a monobloc semented reversed total shoulder artroplasty of Delta Extend type (DePuy, Johnson & Johnson, UK).

**Group 2** is the control group. Patients will be treated surgically with open reduction and internal fixation using the Philos angular stable plate (Synthes, Switzerland) and thread cerclages to secure the tubercles and rotator cuff insertions to the plate. If necessary, judged by the surgeon, a bone substitute or bone graft will be used to enhance stability of the fracture (Norian® or autologous bone graft from the iliac crest).

For both groups the operations will be performed by experienced ortophaedic surgeons well trained within these procedures. In the postoperative treatment early exercises are emphasized in both groups, and will be guided by a specific training protocol recommended to outclinic physiotherapists (Table 1).

**Table 1 Tab1:** **Timeline for physical therapy guideline**

Elements of physical therapy	Reversed prothesis	Philos
	Group 1	Group 2
Anti edema elbow, hand, fingers	Day 1	Day 1
Pendula exercises, passive assisted exercises in forward elevation, extension and abduction.	Day 1	Day 1
Active assisted exercises, Stability exercises and positioning of the scapula	Day 8	Day 5
Active assisted Internal + External Rotation	3 weeks	Day 5
Active exercises. Functional exercises	6 weeks	3 weeks
Isometric resistance	8 weeks	4 weeks
Active strengthening exercises	8 weeks	6 weeks
Functional strengthening exercises and proprioceptive exercises-restore dynamic stability.	12 weeks	8 weeks

